## Abstract

**Background:**

Accurate evaluation of tumor invasion depth is essential to determine the appropriate treatment strategy for patients with superficial esophageal cancer. The pretreatment tumor depth diagnosis currently relies on the magnifying endoscopic classification established by the Japan Esophageal Society (JES). However, the diagnostic accuracy of tumors involving the muscularis mucosa (MM) or those invading the upper third of the submucosal layer (SM1), which correspond to Type B2 vessels in the JES classification, remains insufficient. Previous retrospective studies have reported improved accuracy by considering additional findings, such as the size and macroscopic type of the Type B2 vessel area, in evaluating tumor invasion depth. Therefore, this study aimed to investigate whether incorporating the size and/or macroscopic type of the Type B2 vessel area improves the diagnostic accuracy of preoperative tumor invasion depth prediction based on the JES classification.

**Methods:**

This multicenter prospective observational study will include patients diagnosed with MM/SM1 esophageal squamous cell carcinoma based on the Type B2 vessels of the JES classification. The tumor invasion depth will be evaluated using both the standard JES classification (standard-depth evaluation) and the JES classification with additional findings (hypothetical-depth evaluation) for the same set of patients. Data from both endoscopic depth evaluations will be electronically collected and stored in a cloud-based database before endoscopic resection or esophagectomy. This study’s primary endpoint is accuracy, defined as the proportion of cases in which the preoperative depth diagnosis matched the histological depth diagnosis after resection. Outcomes of standard- and hypothetical-depth evaluation will be compared.

**Discussion:**

Collecting reliable prospective data on the JES classification, explicitly concerning the B2 vessel category, has the potential to provide valuable insights. Incorporating additional findings into the in-depth evaluation process may guide clinical decision-making and promote evidence-based medicine practices in managing superficial esophageal cancer.

**Trial registration:**

This trial was registered in the Clinical Trials Registry of the University Hospital Medical Information Network (UMIN-CTR) under the identifier UMIN000051145, registered on 23/5/2023.

## Background

Esophageal cancer is among the ten most common cancers; it has high morbidity and mortality. Following the National Comprehensive Cancer Network Guidelines, endoscopic resection (ER) is the preferred standard treatment for clinical T1a (cT1a) esophageal cancers without metastasis. However, esophagectomy or chemoradiotherapy (CRT) is recommended for clinical T1b (cT1b) esophageal cancers [1]. ER for esophageal cancers has been extensively developed in Japan and is widely used as a radical treatment. Based on a nationwide clinical survey in Japan, the 5-year overall survival (OS) rates were 88.5% for pathological T1a (pT1a) and 77.9% for pathological T1b (pT1b) cases treated with ER. In contrast, the 5-year OS rate was 83.6% for pT1a and 73.8% for pT1b cases treated with esophagectomy [2]. Therefore, based on these results, Japanese guidelines recommend ER for cT1a-epithelial/lamina propria (EP/LPM) cancers. In addition, ER is considered a viable option for cT1a-muscularis mucosa (MM) and cT1b-SM1, defined as tumors invading the upper third of the submucosal layer [3, 4]. However, for cT1b-SM2-3, esophagectomy or CRT remains the standard treatment. The efficacy of adding CRT after ER in pT1b cancers was confirmed in a non-randomized trial, which demonstrated a favorable 3-year OS rate of 90.7%. Consequently, ER with CRT is considered an alternative treatment for pT1b cancer [5]. Proper differentiation of EP/LPM, MM/SM1, and SM2-3 cancers before treatment is crucial for selecting the appropriate treatment.

Evaluating the preoperative tumor invasion depth using magnifying endoscopy enables the diagnosis of cancer invasion by considering morphological changes in the vessels. To assess tumor invasion depth, the Japan Esophageal Society (JES) proposed a magnifying endoscopic classification (Table 1) [6]. This classification is specialized to discriminate between cancer and non-cancer cases. It helps estimate the tumor invasion depth in cancer cases, specifically for the sub-classification of cEP/LPM, cMM/SM1, and cSM2-3. Type A vessels are diagnosed as non-cancerous, whereas Type B vessels are cancerous. Type B vessels are further classified into types B1, B2, and B3, corresponding to cEP/LPM, cMM/SM1, and cSM2-3. However, previous retrospective studies have revealed that the positive predictive value (PPV) of cEP/LPM as a Type B1 vessel was 92.4%, and that of cSM2 as a Type B3 vessel was 90.7%. However, the PPV of cMM/SM1 as a Type B2 vessel was only 55.7% (27.4% for overestimated pEP/LPM, 55.7% for accurate pMM/SM1, and 17.0% for underestimated pSM2 vessels). This indicates the need to improve the diagnostic accuracy of Type B2 vessels in the preoperative evaluation of tumor invasion depth.

**Table 1 Tab1:** Japan Esophageal Society magnifying endoscopic classification and corresponding depth of invasion

Type of vessels	Definitions	Tumor invasion depth
Type A	Normal intrapapillary capillary loops or abnormal microvessels without severe irregularity	Non-cancerous
Type B	Abnormal microvessels with severe irregularity or highly dilated abnormal vessels	
B1	Type B vessels with a loop-like formation	EP/LPM
B2	Type B vessels without a loop-like formation	MM/SM1
B3	Highly dilated Type B vessels whose calibers appear to be more than thrice that of usual B2 vessels	SM2-3

*MM* Muscularis mucosa, *SM1* Upper third of the submucosal layer, *EP/LPM* Epithelial/lamina propria

Notably, several retrospective studies have been conducted to improve the diagnostic yield of Type B2 vessels in evaluating tumor invasion depth. Studies have found that as the size of the area where Type B2 vessels were observed increased, the pathological tumor invasion depth tended to increase [7, 8]. Consequently, when the observed area was small, the probability of pEP/LPM was high; when the observed area was large, the probability of pSM2-3 was higher. The cut-off values for the tumor invasion depth were 4 mm for pEP/LPM and pMM/SM1 and 10 mm for pMM/SM1 and pSM2-3. In addition, the macroscopic type of the Type B2 vessel area was associated with submucosal invasion. When an elevation (macroscopic type, 0-I) or deep depression (macroscopic type, 0-III) is observed within the B2 vessel area, there is a tendency for pSM2-3 [8]. However, the effectiveness of these additional findings, such as the size of the B2 vessel area and macroscopic type 0-I/0-III in the B2 vessel area, is yet to be confirmed.

This prospective study aims to verify the usefulness of considering the size and macroscopic type of Type B2 vessel area and depth evaluation based on the JES magnifying endoscopy classification in cMM/SM1 cancers.

## Methods

### Study design

This is a multicenter prospective observational study. Endoscopic examinations will be performed in 13 hospitals in Japan. Tumor invasion depth will be evaluated based on only the JES classification (standard-depth evaluation) and the JES classification with additional findings (hypothetical-depth evaluation) for the same patients (Fig. 1). The study protocol will be performed following the Declaration of Helsinki and is approved by the Ethical Review Board of Shizuoka Cancer Center (IRB approval number: T2022–53–2022-1–2). The trial is registered in the Clinical Trials Registry of the University Hospital Medical Information Network (UMIN-CTR) as UMIN000051145. The date of the first registration was 23/5/2023.

**Fig. 1 Fig1:**
[figure not shown]
Patient flow and analyses. CRT, chemoradiotherapy; JES, Japan Esophageal Society

### Study population

Patients who meet all the following inclusion criteria and do not meet any exclusion criteria will be eligible for registration.

#### Inclusion criteria

Diagnosis of histologically confirmed squamous cell carcinoma or clinically diagnosed esophageal squamous cell carcinoma.Clinical T1 esophageal cancer where Type B2 vessels will be observed but Type B3 vessels will not.The part where Type B2 vessels are observed will be considered the tumor’s deepest part.The main sites of the tumor are the cervical, thoracic, and abdominal esophagi [9].The maximum tumor diameter is ≤ 50 mm.Undergoing endoscopic or surgical resection as initial treatment. However, only patients without planned preoperative chemotherapy for overlapping head, neck, or gastric cancer are eligible.No simultaneous esophageal advanced cancer.No history of surgical esophagectomy.No history of radiation therapy to the esophagus, lung field, mediastinum, or treatment for other cancer types.Previous endoscopic resection for esophageal cancer is not a concern. However, the patient is ineligible if the lesion is within 10 mm of the scar from the previous treatment.The age at registration is ≥ 18 years.Performance status will be assessed following the ECOG criteria and should range between 0 and 2. [10]The patient agrees to provide written consent for participation in the trial.

#### Exclusion criteria

Systemic infections requiring treatment.Women who are pregnant, who may be pregnant, or who are breastfeeding.Psychiatric disorders, psychiatric symptoms, or cognitive impairments that make participation in the trial difficult.Other patients who are deemed inappropriate by the registering physician.

### Tumor invasion depth evaluation

#### Standard depth evaluation

Tumor invasion depth will be diagnosed based on the JES classification (Table 1). Specifically, Type B2 vessels are defined as abnormal microvessels with severe irregularity or highly dilated abnormal vessels without loop-like formation." Since previous studies have shown that interobserver and intraobserver agreements for the JES classification were sufficient [11, 12], a central judgment of the JES classification is considered unnecessary in this study. However, typical endoscopic images of Type B2 vessels were confirmed before the study. Type B2 vessel is evaluated where ulcer or erosion is not observed to avoid the effect of B2-mimicking vessels that appear by inflammation [13].

#### Hypothetical depth evaluation

Before initiating the study, we verified the sizes of biopsy forceps available in the market and gained an understanding of the forceps sizes used at each facility. Based on this information, the area of the type B2 vessel will be measured in millimeters using the forceps size as a guide. Measurements < 1 mm will be rounded to 1 mm. If Type B2 vessels are present in multiple areas, then the largest area will be recorded. Macroscopic types are defined following the Treatment Guidelines for Esophageal Cancer [14, 15]. Namely, 0-I is defined as a protruding lesion that is ≥ 1 mm in height, and 0-III is a depressed lesion that is estimated to reach the muscularis mucosa or deeper.

The criteria for judging tumor invasion depth are discussed multiple times by the JES superficial esophageal cancer depth diagnosis criteria study group, and a consensus is reached (Table 2). The anticipated high diagnostic concordance using biopsy forceps as a reference led to the omission of central evaluation in this study.A Lesion with a Type B2 vessel area of ≤ 4 mm is diagnosed as cEP/LPM.A lesion with a Type B2 vessel area of ≥ 10 mm is diagnosed as cSM2-3.I and/or 0-III macroscopic types of the Type B2 vessel area are diagnosed as cSM2-3.When conflicting findings of a B2 vessel area of ≤ 4 mm and 0-I/0-III or Type B2 vessel area are observed in one Type B2 vessel area, the lesion is diagnosed as cSM2-3.When multiple Type B2 vessel areas are observed, the depth is determined based on the deepest finding. Specifically, the order of adoption is 0-I/0-III of Type B2 vessel area, the size of B2 vessel area ≥ 10 mm, the size of Type B2 vessel area between 4 and 10 mm, and the size of Type B2 vessel area ≤ 4 mm.

**Table 2 Tab2:** Criteria for hypothetical depth diagnosis

	Corresponding tumor invasion depth
B2 vessel area ≤ 4 mm	EP, LPM
B2 vessel area between 4–10 mm without additional findings^a^	MM, SM1
B2 vessel area ≥ 10 mm or macroscopic type 0-I/0-III in B2 vessel area	SM2-3

*MM* Muscularis mucosa, *SM1* Upper third of the submucosal layer, *EP/LPM* Epithelial/lamina propria

^a^Additional findings are B2 vessel area ≤ 4 mm, B2 vessel area ≥ 10 mm, and macroscopic type 0-I/0-III in B2 vessel area

### Treatment

Endoscopic resection or esophagectomy should be performed within 12 weeks of upper gastrointestinal endoscopy to minimize the effect of treatment delay on tumor invasion depth. It is considered a protocol deviation if the duration is > 12 weeks.

### Histological evaluation

After endoscopic resection, the specimens will be dissected at 2–3 mm intervals, and the histological tumor invasion depth will be determined. In surgical cases, the specimens will be dissected at intervals of 3 mm whenever possible. Histological diagnoses will be made based on the Treatment Guidelines for Esophageal Cancer [14, 15]. The tumor invasion depth is defined as follows: pEP, cancer remains within the epithelium; pLPM, cancer remains within the lamina propria; pMM, cancer invades the muscularis mucosa; pSM1, cancer remains within 200 μm of the submucosa from the muscularis mucosa; and pSM2, cancer invades beyond 200 μm into the submucosa. Desmin immunostaining is recommended for evaluating the muscularis mucosae.

Esophageal squamous cell carcinoma is a disease encountered daily and is not difficult to diagnose. The handling of specimens is also described in detail in the esophageal cancer handling guidelines; therefore, it is assumed that there is a slight variation in diagnosis between facilities. Therefore, in this study, pathological diagnosis is used to determine the histological depth of esophageal cancer, and no central judgment is performed.

### Registration and data collection

After obtaining written consent from the participants, the trial physicians will register the case on the web built into the UMIN Internet data and information system for clinical and epidemiological research, cloud version (UMIN INDICE cloud, https://www.umin.ac.jp/indice/cloud.html). Participants will be assigned a deidentified number. Data will be collected and stored in the UMIN INDICE cloud using an electronic case record form.

The following data will be collected at the time of registration in a prospective manner: duration of endoscopic observation, model of endoscope used, tumor location, tumor size, macroscopic type, number of areas where type B2 vessels are observed, size of type B2 vessel areas, and macroscopic type of type B2 vessel areas. The following data will be collected after registration: treatment method, en bloc or piecemeal resection, histological type, histological tumor size, size of the resected specimen, histological tumor invasion depth, lymphatic invasion, vascular invasion, resection margin, and presence of lymph node metastasis.

### Endpoints

#### Primary endpoint

This study’s primary endpoint is accuracy, defined as the proportion of cases in which the preoperative depth diagnosis matches the histological depth diagnosis after resection.

#### Secondary endpoints

The secondary endpoints include the following: the proportion of pSM2-3 when the area in which B2 vessels are observed is > 10 mm, the proportion of pSM2-3 when the macroscopic type of the observed B2 vessel area is 0-I or 0-III, the proportion of pSM2-3 when the area in which B2 vessels are observed is > 10 mm or the macroscopic type is 0-I or 0-III, the proportion of pEP/LPM when the area in which B2 vessels are observed is < 4 mm, PPV, sensitivity, specificity, likelihood ratio, a relation between the size of the B2 vessel area and the histological tumor invasion depth, a relation between the number of B2 vessel areas and the histological tumor invasion depth, and the relationship between the macroscopic type of the B2 vessel area and histological tumor invasion.

Furthermore, if the proportion of pSM2-3 when the area in which B2 vessels are observed is > 10 mm, the proportion of pSM2-3 when the macroscopic type of the observed B2 vessel area is 0-I or 0-III, and the proportion of pEP/LPM when the area in which B2 vessels are observed is < 4 mm exceeds 50%, these findings are considered to have an impact on the clinical diagnosis and are therefore included as secondary endpoints.

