#### Analysis of the primary endpoint

The calculation formula for the standard-depth evaluation is: (lesions diagnosed as cMM/SM1 and pMM/SM1 [B]) / (total lesions [A + B + C]) (Table 3), and for the depth evaluation, [(lesions diagnosed as cEP/LPM and pEP/LPM [a]) + ((lesions diagnosed as cMM/SM1 and pMM/SM1 [e]) + (lesions diagnosed as cSM2-3 and pSM2-3 [i]))] / (total lesions [a + b + c + d + e + f + g + h + i]) (Table 4). A point estimate is calculated for accuracy, and a 95% confidence interval is calculated based on the exact binomial distribution. The corresponding *p*-value is also calculated.

**Table 3 Tab3:** Relationship between standard depth evaluation and histological depth diagnosis

	pEP/LPM	pMM/SM1	pSM2-3
cMM/SM1 (B2 vessel)	A	B	C

$$\begin{array}{l}\mathrm{Accuracy}\;\mathrm{of}\;\mathrm{standard}-\mathrm{depth}\;\mathrm{evaluation}\;(\%)\\=(\mathrm{number}\;\mathrm{of}\;\mathrm{lesions}\;\;\mathrm{diagnosed}\;\mathrm{as}\;\mathrm{cMM}/\text{SM}1\;\mathrm{and}\;\mathrm{confirmed}\;\mathrm{as}\;\mathrm{pMM}/\text{SM}1)/(\mathrm{total}\;\mathrm{number}\;\mathrm{of}\;\mathrm{lesions})\times100=\lbrack\text{B}\rbrack/\lbrack\text{A}+\text{B}+\text{C}\rbrack\text{x}100\end{array}$$

*MM* Muscularis mucosa, *SM1* Upper third of the submucosal layer, *EP/LPM* Epithelial/lamina propria

**Table 4 Tab4:** Relationship between hypothetical depth evaluation and histological depth diagnosis

	pEP/LPM	pMM/SM1	pSM2-3
cEP/LPM (B2 vessel area ≤ 4 mm)	a	b	c
cMM/SM1 (B2 vessel area between 4–10 mm without additional findings^a^)	d	e	f
cSM2-3 (B2 vessel area ≥ 10 mm or macroscopic type 0-I/0-III in B2 vessel area)	g	h	i

^a^Additional findings: B2 vessel area ≤ 4 mm, B2 vessel area ≥ 10 mm, macroscopic type 0-I/0-III in B2 vessel area

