
#### Analysis of likelihood ratios

For cases in which the histological tumor invasion depth is obtained after endoscopic resection or esophagectomy, the likelihood ratios will be calculated as sensitivity / (1-specificity) for each additional finding, such as B2 vessel area ≤ 4 mm, B2 vessel area ≥ 10 mm, and macroscopic type 0-I/0-III in the B2 vessel area.

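### The size-based secondary proportions and their 50% criterion use > 10 mm and < 4 mm, whereas the diagnostic rule and every other analysis use ≥ 10 mm and ≤ 4 mm

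*Protocol article*

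**What the plan says.** In the protocol article, the section Hypothetical depth evaluation fixes the rule with inclusive signs: "A Lesion with a Type B2 vessel area of ≤ 4 mm is diagnosed as cEP/LPM" and "A lesion with a Type B2 vessel area of ≥ 10 mm is diagnosed as cSM2-3". Table 2 repeats this. Its footnote lists ≤ 4 mm and ≥ 10 mm as additional findings, so the middle band (cMM/SM1) excludes both end points.

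Table 4, which feeds the primary endpoint, has the same row definitions: "cEP/LPM (B2 vessel area ≤ 4 mm" and "cSM2-3 (B2 vessel area ≥ 10 mm or macroscopic type 0-I/0-III in B2 vessel area". Analysis of likelihood ratios names the findings in the same way: "such as B2 vessel area ≤ 4 mm, B2 vessel area ≥ 10 mm".

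Secondary endpoints differs. It lists "the proportion of pSM2-3 when the area in which B2 vessels are observed is > 10 mm", a combined proportion with the same strict sign or type 0-I/0-III, and a pEP/LPM proportion below 4 mm. It then repeats the strict signs in a criterion, for example "the proportion of pEP/LPM when the area in which B2 vessels are observed is < 4 mm exceeds 50" (per cent), upon which "these findings are considered to have an impact on the clinical diagnosis". In that section > 10 mm appears three times and < 4 mm twice. Neither inclusive sign appears there.

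Analysis of proportion gives only the exact binomial confidence interval and does not restate the cut-offs. No section explains the difference.

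**The concern.** The secondary proportions are there to judge the findings that the rule uses. As written, they judge a narrower set: lesions beyond each cut-off, without those on it. The 50% reading would then be made on lesions that are not quite the ones the rule reclassifies.

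Boundary values are plausible. Size is estimated in millimetres against biopsy forceps, and readings under 1 mm are set to 1 mm. The article does not say that only whole millimetres are recorded, so how often exactly 4 or exactly 10 occurs is unknown.

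The Background section reports that pathological depth tends to increase with the size of the B2 area. On that trend, lesions at exactly 10 mm would be pSM2-3 less often than larger ones, and lesions at exactly 4 mm would be pEP/LPM less often than smaller ones. Leaving them out would then raise both proportions and make 50% easier to exceed. If the signs stay unreconciled, the choice between them could also be made after the data are seen.

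**Working it through.** **1. The plan's own figure.** Sample size calculation gives 121 lesions for an exact binomial test of 50% against 65%, two-sided alpha 0.05, power 90%. With n = 121 the upper critical value is 72, P(X ≥ 72 | 0.50) = 0.0225 and P(X ≥ 72 | 0.65) = 0.912. Power first reaches 90% at n = 114, and 121 is the smallest n from which it stays there (searched up to 299). For dropout, 121 / 0.90 = 134.4, which rounds up to 135. Both stated figures are reproduced. Neither involves a size cut-off, so this point does not touch them.

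**2. The cut-offs side by side.**

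| Place in the protocol article | Lower | Upper |
|---|---|---|
| Hypothetical depth evaluation, Table 2 | ≤ 4 mm | ≥ 10 mm |
| Table 4 (accuracy; PPV, sensitivity and specificity use its cells) | ≤ 4 mm | ≥ 10 mm |
| Analysis of likelihood ratios | ≤ 4 mm | ≥ 10 mm |
| Secondary endpoints, proportions and 50% criterion | < 4 mm | > 10 mm |

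**3. Following boundary lesions through the analyses.**

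- *Exactly 10 mm, no 0-I/0-III.* Called cSM2-3, so it falls in cells g, h or i and counts in accuracy, in the cSM2-3 PPV i/(g+h+i) and in the ≥ 10 mm likelihood ratio. It is outside both the > 10 mm proportion and the combined one.
- *Exactly 10 mm, with 0-I/0-III.* As above, but it does enter the combined proportion and the 0-I/0-III proportion. Only the > 10 mm proportion loses it.
- *Exactly 4 mm, no 0-I/0-III.* Called cEP/LPM, so it falls in cells a, b or c and counts in the cEP/LPM PPV a/(a+b+c). It is outside the < 4 mm proportion.
- *Exactly 4 mm, with 0-I/0-III.* Called cSM2-3 under the conflict rule, so it is not a cEP/LPM lesion at all.

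**4. Size under assumptions.** The article gives no size distribution, so every input here is assumed, and the 50% criterion is read on the point estimate. Let p be the pSM2-3 proportion above 10 mm, q the proportion at exactly 10 mm, and s the share of the ≥ 10 mm group that lies at exactly 10 mm. The inclusive proportion is (1 − s)p + sq.

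| s | p = 0.55, q = 0.20 | p = 0.55, q = 0.30 | p = 0.60, q = 0.30 |
|---|---|---|---|
| 0.10 | 0.495 + 0.020 = 51.5% | 0.495 + 0.030 = 52.5% | 0.540 + 0.030 = 57% |
| 0.20 | 0.440 + 0.040 = 48% | 0.440 + 0.060 = 50% | 0.480 + 0.060 = 54% |
| 0.30 | 0.385 + 0.060 = 44.5% | 0.385 + 0.090 = 47.5% | 0.420 + 0.090 = 51% |

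The criterion stops being met once s reaches (p − 0.50)/(p − q): 0.05/0.35 = 14% in the first column, 0.05/0.25 = 20% in the second and 0.10/0.30 = 33% in the third. So the verdict can flip when the strict proportion is close to 50% and the boundary share is appreciable. Otherwise it does not.

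**The case against.** The strongest reply is that little depends on these signs. Boundary lesions stay in the primary accuracy, PPVs, sensitivity, specificity and likelihood ratios. The cSM2-3 PPV is already the inclusive form of the combined proportion and will be reported as a secondary endpoint. The 50% sentence carries no test or alpha, and it closes by giving the criterion as the reason for listing these endpoints. The study's conclusion rests on accuracy (Planned statistical analyses), read alongside the cMM/SM1 PPV (Discussion). All of this stands, and it limits the point to the size-based proportions and their 50% reading.

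A reader might infer that boundary lesions are lost from the validation of the rule altogether. The tracing above shows that they are not. A reader might also infer that the proportions are demonstrably biased upward. The documents do not support that either: a proportion among lesions above 10 mm is a valid estimate for that group. It is simply a different group from the one the rule defines. The upward shift is plausible from the reported size–depth trend but is not shown, and the flip depends on inputs with no source in the article.

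The reply does not remove the contradiction. The strict signs recur consistently in one section and the inclusive signs everywhere else. The article states both forms, so this is not an effect of condensing a fuller document.

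**Conclusion.** The inconsistency is certain, because it can be read directly from the text. It affects the two single-size proportions, the combined proportion (only for 10 mm lesions without 0-I/0-III) and the 50% criterion. The proportion for 0-I/0-III alone, the primary endpoint, the sample size of 121 (135 with dropout) and the power are untouched.

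The size of the effect cannot be computed. Under the assumptions shown, adding the boundary lesions lowers a 55% proportion by 2.5 to 10.5 percentage points, which may or may not cross 50%. Because a clinical reading is attached to that line, the mismatch is more than clerical, but it does not threaten the trial's main conclusion.

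**What to change.** Before analysis, reconcile Secondary endpoints with Hypothetical depth evaluation, Table 4 and Analysis of likelihood ratios by writing ≥ 10 mm and ≤ 4 mm at all five places in that section, including the 50% criterion. The accuracy, PPVs and likelihood ratios already use this form.

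Also state whether the ≤ 4 mm proportion includes lesions with 0-I/0-III. The diagnostic rule calls those cSM2-3, so changing the sign aligns the cut-off but does not by itself make the ≤ 4 mm group identical to the cEP/LPM group. If they are included, the proportion will differ from the cEP/LPM PPV, and the report should say so.

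The cost is wording only. B2 area size and macroscopic type are already collected at registration, and no sample size or test changes. The proportions may come out slightly less favourable.
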